## **2. STUDY OBJECTIVES**

### **2.1 Primary Endpoints:**

- Seroconversion and seroprotection rates and mean GMT increases in haemagglutination inhibition titres 21-28 days post-immunisation for each of the three included vaccine strains

### **2.2 Secondary Endpoints:**

- Pain scores and subject satisfaction with needleless injection device
- Anti-influenza T-cell responses and kinetics
- Persistence of anti-HA antibody levels and T-cell immunity to influenza
- Cross-protection against drifted influenza strains
- Study of immune cell gene correlates of vaccine immunogenicity and reactogenicity
- Influenza plasmablast frequency at day 7 post-immunization

## **3. STUDY SITES**

The study will be conducted at Flinders Medical Centre (FMC, Adelaide, South Australia) with the option to add additional study sites as required to reach recruitment targets.

## **4. STUDY DESIGN**

This is a Phase 2, randomised, controlled trial of the comparative efficacy of either of two doses of Advax™ adjuvant when combined with 2012 seasonal influenza vaccine as administered by either standard intramuscular injection or a needleless injector device

### **4.1.1. Schedule of study visits**

#### **Day 0 - Visit 1 (All subjects)**

After providing informed consent, and being assessed for eligibility criteria, study subjects will have a medical history taken, baseline clinical assessment, and blood taken for measurement of baseline titres of anti-influenza antibodies. Each eligible subject will then be randomised and receive vaccination with one of the study vaccines. Subjects will be observed for 30 minutes following immunisation and will then be provided with a subject diary to take home with them to record any symptoms or adverse events

#### **Day 1 – By telephone (optional)**

Telephone visit to assess subject reaction to vaccine

#### **Day 7**

Visit to provide blood samples specifically for measurement of influenza plasmablast responses

#### **Days 14 and 21- Substudy subjects only**

Visit to provide blood samples specifically for measurement of B- and T-cell responses. This visit will only involve the subset of subjects who specifically consent to be in the substudy that will involve weekly attendance for 4 weeks for collection of blood.

#### **Day 28 – Final Visit (All subjects)**

Final study visit to provide blood samples and for collection of patient diary. Subjects will have their injection site examined and have any adverse events recorded.

#### **Day 185-365 – By telephone (optional)**

Telephone visit to ascertain subject wellbeing

## **5. ANALYSIS**

### **5.1 Evaluation of vaccine efficacy**

#### **(a) Immunogenicity tests**

1. Anti-influenza antibody titres
2. Anti-influenza B and T-cell responses

### **5.1 Evaluation of vaccine tolerability and safety**

This analysis will utilise the FDA/CBER toxicity grading scale for healthy adult and adolescent volunteers enrolled in preventative vaccine clinical trials ([www.fda.gov/cber/gdlns/toxvac.htm](http://www.fda.gov/cber/gdlns/toxvac.htm)). Specified solicited adverse events will be

collected for 7 days post-immunization and unsolicited adverse events for the total 6 month follow up period.

#### **5.1.2 Elicited Local symptoms/signs**

- ☐ -pain, tenderness, erythema/redness, induration/swelling
- ☐ Vital signs
- ☐ -fever, tachycardia, bradycardia, hypertension (systolic/diastolic), hypotension, increased respiratory rate

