### **7.8.3 Dose limiting toxicities**

Toxicities that must be considered as serious adverse events (SAEs) are:

1. Grade II to IV allergic reactions.
2. Grade IV neutropenia.
3. Grade IV thrombocytopenia.
4. Grade III to IV hypotension.
5. Grade III to IV dyspnea.
6. Occurrence of autoimmune disease.
7. Any Grade IV toxicity (except fever and flu-like symptoms which can be treated with paracetamol).
8. Recurring Grade III toxicities.

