#### **8.5 Follow-up**

The assessments that should be conducted at these visits are given in the Schedule of Assessments. The following evaluations will be performed.

1. Vital signs (blood pressure, heart rate, temperature).
2. Inspection of immunization site
3. Blood sample for influenza antibodies and T-cell responses and safety tests where indicated.
4. Adverse event history.

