### **9.6 Safety analysis**

All adverse events will be summarized and listed with a detailed description, using the MedDRA dictionary. Frequencies of adverse events (number of patients with the event, number of mentions of the event and percentage of patients exhibiting the event) for each vaccine formulation and immunisation route will be given for all adverse events. Adverse events will be summarized by vaccine formulation and immunisation route, body system and relationship to study drug and severity. In addition, listings will be prepared for adverse events leading to treatment discontinuation and for SAEs.

The vital signs (sitting blood pressure, heart rate and temperature) will be presented with summary statistics over the visits and for the change from baseline to endpoint. Individual laboratory variables over the visits and the change from baseline to endpoint will be listed with summary statistics for each dose level. The frequencies of laboratory values below, within and above the relevant normal ranges will be given. The baseline and endpoint laboratory variables will be presented using a contingency table to investigate any range changes. The abnormal and clinically significant laboratory variables will be presented for each patient over the assessments.

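### Section 5.1.2 elicits respiratory rate, pulse and blood pressure abnormalities, but no vital-sign list includes respiratory rate and no pulse or blood pressure reading is named between the dose and the first follow-up visit

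*Protocol*

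**What the plan says.** Under vital signs, Protocol section 5.1.2 lists fever and then "tachycardia, bradycardia, hypertension (systolic/diastolic), hypotension, increased respiratory rate". The introduction to that part of section 5 grades safety on the FDA/CBER vaccine toxicity scale and has solicited events "collected for 7 days post-immunization and unsolicited adverse events for the total 6 month follow up period".

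The measurements are specified elsewhere. Section 8.5 asks for "Vital signs (blood pressure, heart rate, temperature") at follow-up visits. Screening (8.2) and early termination (8.6) name the same three measurements. Section 9.6 analyses the same three: "The vital signs (sitting blood pressure, heart rate and temperature) will be presented with summary statistics over the visits", together with change from baseline to endpoint.

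For the day of vaccination, 4.1.1 says: "Subjects will be observed for 30 minutes following immunisation". Section 10.1.4 adds that staff watch for immediate adverse events during that time. Neither place names a reading. The Day 7 entry in 4.1.1 is: "Visit to provide blood samples specifically for measurement of influenza plasmablast responses". Section 7.8.3 includes "Grade III to IV hypotension" among the toxicities to be handled as serious adverse events.

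**The concern.** Safety and tolerability are primary endpoints, and the comparison of interest is between adjuvant doses and unadjuvanted vaccine. Five of the six signs in 5.1.2 (all except fever) can be graded only from a pulse, blood pressure or respiratory rate reading. If the readings are not taken when a vaccine reaction would be expected, the protocol promises an assessment that its own procedures do not supply. An analysis plan written later cannot recover readings that were never collected. At stake is whether the report can say anything comparative about acute vital-sign changes by arm, and whether a lack of recorded events could be mistaken for evidence that none occurred.

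**Working it through.** The protocol gives no figure to reproduce, so the check sets the sections side by side. Fever is left out because temperature is in every list.

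**Step 1. Is each elicited sign covered by a measurement list?**

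| Section | Blood pressure | Pulse | Respiratory rate |
|---|---|---|---|
| 8.2 Screening | yes (supine) | yes | no |
| 8.5 Follow-up | yes | yes | no |
| 8.6 Early termination | yes | yes | no |
| 9.6 Safety analysis | yes (sitting) | yes | no |

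Respiratory rate is in 0 of 4 lists. The systemic examination items in 5.1.4 (fever, fast pulse, raised blood pressure) do not include it, and the diary items in 10.1.4 are symptoms only.

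**Step 2. What is named between the dose and the first follow-up visit?**

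- Day 0: 30 minutes of observation (4.1.1, 10.1.4), with no reading named.
- Day 1: an optional telephone call, at which staff can measure nothing.
- Diary: symptoms, with no pulse, blood pressure or respiratory rate.

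Named pulse or blood pressure readings in this interval: 0.

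**Step 3. When does the first post-dose reading fall?**

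Section 5.3 allows 7 days either side of a scheduled visit, so Day 7 runs from 7 − 7 = Day 0 to 7 + 7 = Day 14. If the 8.5 assessments apply at Day 7, the first reading may be taken up to 14 − 7 = 7 days after solicited collection closes and still be in window.

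If the Day 7 entry in 4.1.1 is taken literally as blood sampling only, the next visit for all subjects is Day 28, in window from 28 − 7 = Day 21 to 28 + 7 = Day 35. That is entirely outside the solicited period. The Day 14 and Day 21 visits are for substudy subjects only and are also described as blood sampling. Sections 4.1.1 and 8.5 do not say which reading is meant.

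**Step 4. What is the baseline?**

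The pre-treatment list in 8.4 has a physical evaluation but does not itemise vital signs, and the Day 0 entry in 4.1.1 mentions only a baseline clinical assessment. The only itemised pre-dose set is at screening, which may be up to 28 days earlier. Blood pressure is supine there and sitting in 9.6. A change from that baseline to endpoint does not isolate an acute effect of the injection.

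**Step 5. How many subjects are affected?**

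Section 9.7 plans 6 groups of 65, so 6 × 65 = 390 (the stated ceiling is 400). The gap is the same in every group.

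**The case against.** A reader might infer that acute vital-sign reactions, including the hypotension in 7.8.3, could not be detected at all. The documents do not support that. Staff monitor subjects for 30 minutes, adverse events are collected at each visit, and 5.1.3 elicits any need for medical care, an emergency visit or a hospital stay. A symptomatic or severe reaction has several routes to being recorded. Section 7.8.3 concerns only the higher grades of hypotension. For events without a toxicity-scale grade, 10.1.6 defines severe by inability to carry on as usual. The scale's numerical cut-offs are not in the protocol, so whether such an event could be silent cannot be settled here.

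A reader might also infer that the five signs would be tabulated at near zero in every arm. That too goes beyond the text. Section 9.6 summarises vital signs by visit, and nothing says that an unmeasured sign will be counted as absent. The risk of misreading is real, but it is not a stated analysis.

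Three further objections carry weight:

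- Sections 8.4 and 8.5 refer to a Schedule of Assessments that is not in the text at hand. It may add readings.
- The Day 7 entry in 4.1.1 need not exclude other assessments: 8.7.2 also takes antibody samples then, and 8.5 covers follow-up visits generally.
- Section 5.1.2 sits under Analysis and could be a list of grading categories, not a measurement schedule.

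The first two limit certainty about timing. The third does not remove the problem, because a grading category with no values behind it cannot be used. None of the three explains why 9.6 omits respiratory rate while 5.1.2 elicits it.

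**Conclusion.** The point holds as an inconsistency between what the protocol elicits and what it measures. Respiratory rate is an elicited sign found in 0 of 4 vital-sign sets, including the analysis section. The text names 0 pulse or blood pressure readings between the dose and the first follow-up visit, which may fall as late as Day 14, or Day 35 if Day 7 is for blood sampling only. As written, respiratory rate is not measured or analysed, and mild or asymptomatic acute changes in pulse and blood pressure cannot be systematically graded or compared between arms. Detection of symptomatic or severe reactions is not in question.

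The conclusion rests on the narrative text being complete. If the Schedule of Assessments lists readings on Day 0 after the dose, the timing part falls away, but 5.1.2 and 9.6 would still disagree on respiratory rate. The gap touches a primary safety assessment in every subject and is inexpensive to close, so it is worth correcting.

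**What to change.** Reconcile 5.1.2 with 8.2, 8.5, 8.6 and 9.6:

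1. Add respiratory rate to the four vital-sign sets.
2. Record the elicited vital signs just before dosing and once at the end of the existing 30-minute observation.
3. Add to 9.6 a summary of that pre-dose to post-dose change by arm.
4. State in 4.1.1 whether the 8.5 assessments apply at Day 7.

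If these readings are not wanted, remove from 5.1.2 the signs that will not be measured, so that they are not reported as absent. The Schedule of Assessments should be checked against whichever option is chosen.

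The first option costs a few minutes per subject while the subject is already on site, plus case report form fields and protocol wording. The second costs wording only, but gives up any systematic statement on the signs removed.

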#### **5.1.3 Elicited Systemic (general) symptoms/signs**

- ☐ Nausea/vomiting, diarrhoea, headache, fatigue, myalgia
- ☐ Interference with activity, need for medical attention, ER visit/hospitalisation

#### **5.1.4 Physical examination**

Local - inflammation, induration, redness, granuloma, skin breakdown

Systemic - Fever, tachycardia, hypertension

### **5.2 Choice of control groups and blinding**

This is a randomized, controlled Phase 2 study. A total of up to 400 subjects will be recruited for the study, and randomly assigned on a one to one to one basis (1:1:1) to standard TIV, TIV + Advax 5mg or TIV + Advax 10mg. All subjects will also be randomised on a 1:1 basis to receive the immunisation via needle and syringe or Pharmajet needleless injector device. There will therefore be 6 subgroups in total.

As the vaccine containing Advax is a cloudy white colour whereas TIV is a clear solution, it is not possible for the staff administering the vaccine to be blinded. Subjects will be blinded and will not be informed which vaccine they receive. Similarly, where a trial adverse effect requires assessment, this will be performed by a blinded adjudicator. All laboratory tests will be performed blinded.

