### **5.4 Safety Monitoring Board**

Given the short duration of this study and the fact that just a single immunization will be given on study day 0, a safety monitoring board (SMB) is not deemed suitable for this study. The Principal Investigator will monitor all serious adverse events and if considered to be related to study medication this will be notified to the ethics committee.

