#### **7.7.3 Accountability of study vaccine**

All vaccine supplies for this study should be retained in a safe secure place at all times during the study. The investigational product(s) should be administered by the investigator, or by a qualified individual under the investigator's supervision. An up to date vaccine inventory/dispensing record must be maintained. The individual's ID number and initials should be written on each vial just before it is administered to an individual. The empty or partially empty vials must then be stored, so that the vials administered to each individual can be verified by the study monitor. After completion of the study, all unused material must be accounted for. If the investigator or hospital pharmacist destroys the supplies, written documentation is mandatory. The record must include the following: who destroyed the supplies, the identity and quantity of what was destroyed, and the method and date of destruction. All drug supplies must be accounted for. At the end of the study, a copy of the vaccine inventory/dispensing record should be stored and a copy kept in the investigator's study file. The investigator is responsible for the vaccine supplies.

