### **9.10 Randomisation procedure**

Random allocation sequences will be generated by an independent source. . Randomisation codes will be held independently to the site. To randomise a subject the investigator or study co-ordinator will use an on-line interface to enter subject initials and date of birth. On entering this data, they will be issued with the next available randomisation code for the particular randomisation block or category to which the entered subject belongs, e.g. with or without Advax, 10mg or 20mg etc.

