### **10.1.4 Methods of recording and assessing adverse events**

All adverse events must be documented in the section of the CRF reserved for this purpose and not in remarks elsewhere in the CRF. The following aspects must be recorded

- The onset.
- Where applicable, the end of the adverse event.
- A description of the adverse event.
- Any factors considered as possibly promoting the occurrence of the adverse event.
- Concomitant medication.

An assessment by the investigator of the causality; the decisive factor in the documentation is the temporal relationship between the adverse event and the study drugs. The following judgments of the causal relationship are possible: none, remote, possible, probable and not assessable. If, in any individuals, the same adverse event occurs at several investigational times, then the adverse event in question must be documented and assessed anew each time.

Participants will be monitored by study staff for 30 min after immunization for any immediate adverse events and by the subjects themselves using a symptom diary for 28 days post immunization. Participants will be instructed to assess specific injection site adverse events (redness, swelling, warmth, tenderness, pain with arm movement) and systemic adverse events (chills, headache, muscle aches, fatigue, nausea, vomiting, diarrhoea, joint pain), all reports of other adverse events will be collected and categorized by body system. Adverse events will be collected by study personnel at each visit.

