### **10.3 Monitoring of individuals with adverse events**

Each individual must be carefully monitored for adverse events. Assessment must be made of the seriousness, intensity and relationship to the administration of the study drug. In case of an adverse event, the investigator will decide if the study will be continued or terminated for the individuals. In case of an SAE, the study drug will be stopped, the individuals will receive appropriate treatment, and the individuals will be closely observed until reversal of the event and stabilization of the subject.

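### Section 5.2 promises a blinded adjudicator for adverse events, but 10.1.4 and 10.2 give causality and the assessment of serious events to an investigator who need not be blinded, and nothing says whose rating is analysed

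*Protocol*

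**What the plan says.** Section 5.2 explains that the adjuvanted vaccine looks different from plain TIV, so "it is not possible for the staff administering the vaccine to be blinded". Subjects are to be blinded and laboratory tests run blinded. For adverse events the safeguard is that "where a trial adverse effect requires assessment, this will be performed by a blinded adjudicator".

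The sections that direct the safety work do not mention that adjudicator:

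- Section 10.1.4 lists, among the items for each event, "An assessment by the investigator of the causality".
- Section 10.2, on reporting of SAEs, has the investigator document and medically assess the event.
- Section 10.3 says "Assessment must be made of the seriousness, intensity and relationship to the administration of the study drug", without naming the assessor. Section 10.1.6 requires a severity grade, also without naming who gives it.
- Section 5.4 states "The Principal Investigator will monitor all serious adverse events and if considered to be related to study medication", the ethics committee is to be notified. It does not say who does the considering.

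On who may know the allocation, 7.7.3 says the product "should be administered by the investigator, or by a qualified individual" under supervision, and 9.10 says "the investigator or study co-ordinator will use an on-line interface" to obtain the randomisation code.

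**The concern.** Frequency and severity of adverse events are a primary variable (9.1.1), and 9.6 summarises events by relationship to study drug and by severity for each formulation. Tolerability relative to TIV alone is part of the primary objective.

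Causality is the most subjective of these ratings, and it is the one that section 10 expressly gives to the investigator. If that person drew up or injected the vaccine, or entered the subject for randomisation, the rating may be made with knowledge of the arm. This could create a difference in related events between formulations, or hide one. Statistical analysis cannot restore blinding once the ratings have been made.

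**Working it through.** No figure in the protocol needs reproducing. The check is a comparison of who does what.

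| Task | Section | Person named | Blinding required? |
|---|---|---|---|
| Assessing adverse effects that need assessment | 5.2 | Adjudicator | Yes |
| Causality of an event | 10.1.4 | Investigator | Not stated |
| Medical assessment of a serious event | 10.2 | Investigator | Not stated |
| Seriousness, intensity, relationship | 10.3 | Nobody | Not stated |
| Severity grade | 10.1.6 | Nobody | Not stated |
| Monitoring of SAEs | 5.4 | Principal Investigator | Not stated |
| Judging an SAE related | 5.4 | Nobody | Not stated |
| Injection-site examination | 4.1.1 (Day 28), 8.5 | Nobody | Not stated |
| Giving the vaccine | 7.7.3 | Investigator, or a qualified person under supervision | Cannot be (5.2) |
| Obtaining the randomisation code | 9.10 | Investigator or co-ordinator | Not stated |

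1. Causality has two named assessors, the adjudicator in 5.2 and the investigator in 10.1.4. Nothing ranks or links them.
2. For serious events, 10.2 again names the investigator, though it does not mention severity.
3. The investigator named in 10.1.4 and 10.2 is a role that 7.7.3 allows to vaccinate. No text keeps the two tasks apart for a given subject.
4. Section 9.6 uses relationship and severity but does not say whose ratings.
5. Solicited symptoms follow another route. Subjects record them in a diary for 28 days (10.1.4), and subjects are to be blinded (5.2). Section 9.6 also classifies measured local reactions and fever by fixed limits (10 mm and 50 mm, 38°C and 39°C). What remains exposed is causality, severity of unsolicited and serious events, and the staff examination of the site.

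For scale only, here is an illustration that is not a planned test. Section 9.7 gives 65 per group, and each formulation is given by two routes, so 2 × 65 = 130 per formulation. Assume no true difference, a recorded rate p under TIV, and a recorded rate p + d under one adjuvanted formulation because the assessor knows the arm. Both p and d are assumptions without a source in the protocol. The chance of a two-sided Fisher result below 0.05 is

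Σ Bin(x; 130, p) × Bin(y; 130, p + d), summed over all (x, y) for which Fisher's p < 0.05.

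| p | d = 0 | d = 3 points | d = 5 points | d = 10 points |
|---|---|---|---|---|
| 10% | 3.0% | 8.3% | 17.8% | 56.0% |
| 20% | 3.5% | 6.9% | 12.9% | 40.9% |
| 30% | 3.7% | 6.3% | 11.1% | 34.3% |

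A shift of 5 points is 0.05 × 130 = 6.5 subjects rated differently in one formulation. Only upward shifts are shown; a downward shift could mask a real difference.

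**The case against.** The best defence is that 5.2 already provides the safeguard. Its wording can be read as referral of selected events to the adjudicator, on top of routine recording by the investigator. Collecting events at visits, monitoring SAEs and notifying the ethics committee are not assessments, so they do not conflict with it. A qualified person other than the investigator may do all the injecting. Much of the safety comparison is also protected, by blinded self-report, fixed size and temperature limits, a published toxicity scale and blinded laboratory work.

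Most of this stands, and it limits the point. It does not remove it. If adjudication is selective, the protocol does not say which events are referred or whose view prevails, while 10.1.4 asks for the investigator's causality judgement without restriction. That the investigator might not vaccinate is a possibility, not a requirement.

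A reader might infer more: that 5.4, 10.1.4 and 10.3 together hand both causality and severity to an unblinded investigator. The text does not support that. Only 10.1.4 gives causality to the investigator. Sections 5.4 and 10.3 are in the passive on who judges, and none of the three assigns severity to anyone. Nor does any section say that the assessing investigator is in fact unblinded.

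The illustration should not be over-read either. The Fisher comparisons in 9.6 concern the proportion with a reaction by vaccine group, observation period and severity. Relationship appears only in the descriptive summaries.

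**Conclusion.** The point holds in a limited form. Sections 5.2 and 10.1.4 name different assessors of causality, 10.2 adds the investigator for serious events, and nothing requires that investigator to be blinded or says whose rating is analysed. A site following section 10 as written could put unblinded causality ratings into the 9.6 tables.

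The whole primary safety comparison is not compromised. The exposure covers causality, severity of unsolicited and serious events, and staff-examined injection sites. For severity it rests on the assessor being unnamed in 10.1.6 and 10.3, and on the general medical assessment in 10.2. Solicited symptoms are less exposed as long as subjects stay blinded.

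The protocol offers nothing from which to estimate the bias. Under the stated assumptions, a 5-point shift would raise the false-positive probability from 3.0–3.7% to 11.1–17.8% over base rates of 10% to 30%. That shows only that a modest shift would matter at this sample size. The conclusion rests on the contradiction, not on those figures.

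**What to change.** Reconcile 5.2 with 10.1.4 and 10.2, and carry the wording into 9.6:

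- State that the causality ratings, and the severity ratings of unsolicited and serious events, used in the 9.6 tables are those of the blinded adjudicator already named in 5.2.
- Keep the investigator's own rating for expedited reporting, so that reporting does not wait for adjudication.
- State that the Day 28 injection-site examination is done by existing staff who did not prepare or give that subject's vaccine.

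This needs no new role. The cost is more events for the adjudicator to review than 5.2 may have intended, some rostering at Day 28, and a protocol amendment. It has to be in place before ratings are made.
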